## Background

Breast conserving surgery (BCS) is carried out since the late seventies of the former century. Studies with more than 20 years of follow up have shown its equivalency to mastectomy with regard to loco regional control and overall survival [1–4]. Currently, the majority of woman with breast cancer (50–70%) is treated with BCS [5]. Apart from oncological adequate resection achievement of a good cosmetic result and high patient satisfaction are essential components of successful BCS. Psychological morbidity due to disfigurement following surgery for breast cancer therapy in patients were first reported in the early fifties [6]. However more thorough studies on QoL (psychosocial, physical and sexual well-being) originate only form the last 2 decades. This growing awareness for preservation of body image, cosmetic result and QoL is attenuated by the increasing prevalence of patients who survive breast cancer [7].

Today, some 30–40% of the patients report that they are disappointed with the final cosmetic result of BCS [8]. Breast asymmetry after BCS is significantly correlated with poor psychosocial functioning and fear of recurrence, which has negative impact on QoL [8, 9]. Poor cosmetic result is caused by contour defects, asymmetry of the breasts, malposition of the nipple, adhesions, and retractions due to large resection volumes, which can be attenuated by subsequent radiation therapy [10]. Tumor to breast ratio as well as localization of the tumour is accepted factors with regard to the risk to obtain an unsatisfactory cosmetic result. Several studies have reported that cosmetic failure rates are significantly higher when the tumour is located in the inner half of the breast, if lumpectomy volume exceeds > 20% of the breast or more than 50–85 ml regardless of the size of the breast [11–14].

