Both Audretsch and Gabka first introduced oncoplastic breast conserving surgery in the early nineties [15–17]. In order to prevent breast deformity many different oncoplastic techniques have been proposed to reshape and/or modify the appearance of the breast. Clough et al. described several of these oncoplastic surgical techniques in a quadrant-per-quadrant atlas [18]. Oncoplastic surgery (OPS) incorporated in BCS involves reconstruction of the resection defects by volume displacement techniques using adjacent breast tissue. With regard to volume displacement techniques 2 levels of OPS are recognized, based on the extent of the resection and the corresponding mammoplasty techniques [18]. Level I OPS includes local re-arrangement of volume defects of < 10%, and level II OPS includes the volume displacement technique for volume defects of more than 10–30% volume.

Recognizing the risk of a potentially unfavourable cosmetic outcome is the first step in deciding when to incorporate OPS in BCS. Application of OPS is reported to expand the possibility of BCS thereby still achieving acceptable or good cosmetic results and QoL [19]. On the contrary, in a small subgroup of a recent Dutch retrospective study in 125 patients (74% BCS and 26% OPS) it was suggested that patients in whom conventional BCS was carried out scored significantly better than those treated with OPS when scored by BCCT.Core cosmetic result scoring software [20].

The exact role as well as the extent of OPS in BCS in order to ameliorate cosmetic outcome, patient satisfaction and quality of life remains rather ill defined. The former is partly due to lack of high quality studies on this issue.

In order to identify factors that affect cosmetic outcome and influence QoL a standardized method to evaluate cosmetic result is warranted. Currently, different methods are used to evaluate the cosmetic result of BCS, including panel evaluation using a photo scoring method, computer programs that objectively and automatically evaluate breast aesthetics by using patient photographs (BCCT.Core), the breast retraction assessment to measure breast asymmetry and patient opinion using QoL forms [21–24].

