#### Diagnostics and treatment characteristics

Baseline characteristics including oncologic data will be collected of all patients containing information about histology, volume of the breast, hormone receptor status, tumour location and tumour size on magnetic resonance imaging (MRI), amount of removed breast tissue during lumpectomy, axillary surgery, re-excision, adjuvant radiotherapy and hormone therapy.

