### Statistical analysis

Raw data summaries of patient, tumour and treatment characteristics will be made by operation type. Spearman’s correlation and Pearson’s correlation will be used in a descriptive way to assess the correlation of the mean score of total expert panel score, total patient score and automated calculations of the BCCT.Core software. Cosmetic result and quality of life will be measured at *T* = 0, *T* = 1 and *T* = 2. Difference in (changes from baseline of) satisfaction of cosmetic results will be compared between patients undergoing BCS without OPS with those with OPS using linear mixed modelling, with adjustment made for the baseline (*T* = 0) measurement of cosmetic scoring and for other potentially confounding factors such as age, location, size of the tumour and re-operation. The quality of life instruments (EQ5D5L, BREAST-Q, EORTC QLQ C30 and EORTC QLQ BR23) will be analysed similarly after using the prescribed scoring methods when appropriate. The partial correlation of the level of the cosmetic results with the baseline level of each of the quality of life instruments will be analysed after adjustment for operation type. At *T* = 1 and *T* = 2 the partial correlation will be analysed after adjustment for operation type and the baseline level of both the cosmetic result and the quality of life instrument at hand, so as to assess the correlation between changes at *T* = 1 and *T* = 2 from what is known at *T* = 0. Effect of resection volume on the cosmetic score at *T* = 1 and *T* = 2 will be analysed using linear mixed modelling with adjustment for the potentially confounding effects of baseline cosmetic score, age, education, body mass index, tumour quadrant, operation type, possible re-operation and/or complications.

All statistical analysis will be performed with SPSS version 23.0 from IBM Software.

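### The secondary resection-volume model leaves out breast volume, which the trial collects; add it with its interaction and report percentage resected alongside.

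*Protocol article*

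**What the plan says.** The Statistical analysis section plans a separate explanatory model: "Effect of resection volume on the cosmetic score at *T* = 1 and *T* = 2 will be analysed using linear mixed modelling". It adjusts for "baseline cosmetic score, age, education, body mass index, tumour quadrant, operation type, possible re-operation and/or complications". The list is enumerated. By contrast, the comparison of surgery with and without OPS, described earlier in the same section, gives its confounders only as examples. No unit is given for resection volume. An absolute amount is the natural reading, because the Diagnostics and treatment characteristics section records the "amount of removed breast tissue during lumpectomy". That section also records breast volume, in a list that runs "histology, volume of the breast, hormone receptor status, tumour location and tumour size on magnetic resonance imaging (MRI".

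Elsewhere the article relates volume to breast size in several ways:

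- **Background, risk factors:** "Tumor to breast ratio as well as localization of the tumour is accepted factors".
- **Background, limits:** cosmetic failure is said to be more frequent for inner-half tumours or "if lumpectomy volume exceeds > 20% of the breast or more than 50–85 ml regardless of the size of the breast". The Discussion repeats both volume limits.
- **Background, levels:** level I covers defects under 10%, while "level II OPS includes the volume displacement technique for volume defects of more than 10–30% volume".
- **Treatment allocation:** the surgeon's choice takes breast size and the breast/tumour ratio into account, and OPS is generally recommended above an expected 10% of breast volume.

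**The concern.** By the article's own account, breast size influences the choice of technique, and relative resection size is one route to a poor cosmetic result. If breast size also goes with the amount removed, overall or among women with the same operation type, it confounds the resection-volume slope. It may also modify the effect, since a fixed amount is a larger share of a small breast.

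The planned covariates deal with this only in part. BMI is a loose proxy. Operation type carries percentage information, but coarsely: there are three categories, and the article says the choice is not strictly defined and depends on surgeon preference. Conditioning on operation type can even strengthen the link between amount removed and breast size. Among women with similar percentages, those with more tissue removed tend to have larger breasts.

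At stake is how the volume effect can be interpreted. The article cites a relative and an absolute limit, and a model without breast size cannot tell which the trial's data support.

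**Working it through.** **The plan's own figure.** The article gives no figure for this model. Its one calculated figure, the sample size, reproduces. With n = 2(z₁₋α/₂ + z_power)²(SD/Δ)², α = 0.027, SD 16 and Δ 8:

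- 80% power: 2 × (2.21 + 0.84)² × 4 ≈ 74.4, so 75 (stated 75).
- 90% power: 2 × (2.21 + 1.28)² × 4 ≈ 97.4, so 98 (stated 100, which is on the safe side).

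The present point does not touch it.

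**Amount against share.** Percentage = 100 × amount / breast volume. The amounts are the article's 50 and 85 ml. The breast volumes are assumptions, because the article gives none.

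| Amount | 300 ml breast | 500 ml | 800 ml | 1200 ml |
|---|---|---|---|---|
| 50 ml | 16.7% | 10.0% | 6.2% | 4.2% |
| 85 ml | 28.3% | 17.0% | 10.6% | 7.1% |

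The same amount can fall on either side of the article's 10% line. At 85 ml it can also fall on either side of 20%.

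**Why an interaction is needed if harm follows share.** Suppose the score falls b points per percentage point. For breast volume B, the slope per 10 ml is then −b × 1000/B. With b = 1 this is −3.3 points at B = 300 ml and −1.1 at B = 900 ml. One common slope describes neither.

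**Illustrative simulation.** All inputs except the SD of 16 are assumed:

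- 200,000 patients per scenario; one outcome time, fitted by ordinary least squares.
- Log-normal breast volume, median 700 ml, log-SD 0.5.
- Resection with median 50 ml and log-SD 0.5 at a given breast volume, rising with breast volume at elasticity 0, 0.5 or 0.8.
- BMI correlated 0.3, 0.5 or 0.7 with log breast volume.
- Operation type assigned from a noisy version of percentage resected.
- Truth: 1 point lost per percentage point.

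The model contains amount, BMI and operation type, without or with log breast volume. Loss = 1 − (slope without / slope with).

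| BMI correlation | Elasticity | Slope per 10 ml, without | With | Loss |
|---|---|---|---|---|
| 0.3 | 0 | −1.10 | −1.61 | 32% |
| 0.3 | 0.5 | −0.52 | −1.12 | 54% |
| 0.3 | 0.8 | −0.43 | −0.90 | 52% |
| 0.5 | 0 | −1.18 | −1.63 | 28% |
| 0.5 | 0.5 | −0.59 | −1.14 | 48% |
| 0.5 | 0.8 | −0.45 | −0.87 | 48% |
| 0.7 | 0 | −1.28 | −1.61 | 21% |
| 0.7 | 0.5 | −0.72 | −1.14 | 37% |
| 0.7 | 0.8 | −0.56 | −0.87 | 36% |

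Other assumed inputs (mean breast volume 600–700 ml, coefficient of variation 0.5–0.6, resection about 60 ml) gave 15% to 29% when resection volume was unrelated to breast size. They gave 28% to 59% when larger breasts had larger resections.

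Two further checks on the first grid:

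- **Without operation type.** At elasticity 0 the loss disappears (slope about −1.6 with or without breast volume). In those scenarios the bias comes from conditioning on operation type. At elasticity 0.5 or 0.8 a loss of 20% to 39% remains.
- **Truth in absolute volume.** If the score instead falls 1 point per 10 ml whatever the breast size, the slope is about −1.0 with or without breast volume in all nine scenarios. The bias is nil.

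**The case against.** Four points can fairly be made for the plan.

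1. **Absolute volume has a stated rationale.** A reader might infer that the protocol regards the tumour-to-breast ratio as decisive, so that an absolute exposure contradicts it. The text does not support that. The ratio is named beside tumour location as an accepted factor, and the Background and Discussion both cite 50–85 ml irrespective of breast size. This stands, and it is why absolute volume should be kept. But checking whether a limit holds irrespective of breast size requires breast size in the model.

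2. **The covariates carry some breast-size information.** A reader might infer that equal amounts from small and large breasts are treated as the same exposure. That is true only at equal BMI, operation type and other covariates. This stands as a limit on the claim, but both proxies are partial, and operation type can add to the bias.

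3. **The simulated loss is built in.** Assuming harm per percentage point guarantees that an absolute slope without breast volume looks poor. This stands. The figures show what happens if that assumption holds and are not evidence that it does.

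4. **The analysis is secondary.** A reader might infer that this model will set a volume threshold for the planned decision tool, and that any such cut-off would be wrong. No section says so. No cut-off analysis is described, and the Discussion bases the decision tree on patient and tumour characteristics in general. This stands and limits the consequence.

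The exact definition of resection volume may lie in a fuller document. The covariate list, however, is set out here and omits a collected variable that the article's own reasoning makes relevant.

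**Conclusion.** The point holds as an omission from a secondary explanatory model. The listed covariates leave out breast volume, a plausible confounder and effect modifier that the trial already measures, and BMI and operation type replace it only partly.

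The size of the bias is uncertain. If harm follows the share of the breast removed, the illustrative slopes are roughly 15% to 55% too small, with 59% at the extreme of one set of inputs. If harm follows absolute volume, there may be no bias. These figures rest on assumed breast volumes, resection sizes, correlations and harm per percentage point, and on a simplified model without the remaining planned covariates or the repeated measurements. The documents support neither an unconditional statement that the slope is attenuated nor the view that absolute volume is the wrong exposure.

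The comparison of operation types on the 4-week cosmetic score and its sample size are unaffected.

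**What to change.** Amend the sentence on resection volume in the Statistical analysis section:

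- Keep absolute resection volume as an exposure and state its unit.
- Add breast volume and its interaction with resection volume to the covariates.
- Report a parallel analysis with percentage resected (100 × amount removed / breast volume) as the exposure.
- Report each analysis with and without operation type, because OPS level is itself defined by percentage and conditioning on it changes what the slope means.

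Together these analyses let the trial examine both the relative and the absolute limit that the article cites. The cost is one or two extra model terms, some collinearity of breast volume with BMI, resection volume and operation type (hence wider intervals), and a few more lines of reporting. Both measurements are already collected.

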### Adverse events

No adverse events as a result of this study are expected, as patients do not undergo any additional interventions. If any adverse events of one of these surgical methods are identified they will be reported to the medical ethical commission and hospital board.

### Protocol changes

Important protocol modifications will be first submitted to a medical ethical commission and the hospital board. In case of approval all participants and the Dutch trial register will be informed.

## Discussion

The COSMAM Trial is a first prospective cohort study that aims to define the role of different levels of additional OPS in BCS for breast cancer patient. This study compares objective and subjective scoring systems prospectively and is approved by a Dutch medical ethical board.

Since randomization for this type of surgery is virtually impossible the study observes the results of daily practice. This will give a real world experience of current breast saving treatment in an oncological breast cancer centre with multiple surgeons performing different levels of OPS in different patients according to their personal preference. We do realize that in the ideal setting patients with similar tumour types in the same quadrant of the breast should preferably be randomized between lumpectomy with oncoplastic surgery and conventional lumpectomy. However from both an ethical and practical point of view we feel that carrying out such a study could possibly affect cosmetic result and quality of life. Especially in patients with an expected removal of > 10% of the total breast volume as well as large lesions in the upper medial and lower medial and lower lateral quadrants. Based on the reports that application of OPS expands the possibility of BCS thereby still achieving acceptable or good cosmetic results and QoL [19]. Without OPS in these patients a mastectomy would be considered because of high chance of deformation of the breast performing a standard lumpectomy.

All patients who are scheduled for BCS are asked to participate in this study. Our study population is considered to be representative a reflection of the Dutch community.

Despite literature describing the use of OPS there is no clear international standard describing the indications for application of different levels of OPS neither which technique is indicated in relation to the tumour site and the density of the breast tissue. Based on current literature OPS is recommended in patients with a tumour situated in the inner half of the breast, when lumpectomy exceeds > 20% of total breast volume or more than 50–85 ml, regardless of the size of the breast [11–14, 27]. The techniques that are currently used and to what extent they are carried out mainly depends on the surgeon’s preference and expertise.

To implement OPS as a standard additional technique in BCS more data are needed regarding the clinical value of which patients benefit from OPS, thereby not only taking into account tumour characteristics and location but also type of breast tissue and opinion of the patient. The aim of the COSMAM trial is to assess the additional value of different levels of oncoplastic BCS, with regard to QoL and cosmetic outcome by objective measurements of the final cosmetic result in comparison with patients undergoing conventional BCS. The patient and tumour characteristics correlated with a satisfying cosmetic result and QoL after OPS may give valuable information for development of decision-making tree when to use OPS and which technique will give the most satisfying and oncologic safe result.

The implementation of a decision-making tree for the indication of OPS follows the trend of adjusting breast cancer treatment to tumour type and location as well as specific patient characteristics. By personalizing BCS we will not only focus on the medical treatment of breast cancer patients but also on individual specific needs and personal preferences of the patient as a human being.

## Conclusion

The purpose of this prospective study is to assess the clinical value of addition of different oncoplastic techniques in breast conserving surgery, with regard to quality of life and cosmetic outcome by objective measurements of the final cosmetic result in comparison with standard breast conserving surgery. The results of this study can be used for development of a clinical decision model to guide the use of oncoplastic breast techniques in order to establish personalized oncologic safe and cosmetic satisfying breast conserving treatment.

## Abbreviations

BCS: Breast Conserving Surgery
BMI: Body Mass Index (length^2^/weight)
ER: Estrogen Receptor
Her2Neu: Human Epidermal Growth Factor Receptor 2
LR: Local recurrence
LRFS: Local recurrence free survival
MRI: Magnetic Resonance Imaging
OPS: Oncoplastic Breast Conversing Surgery
pBAD: Relative breast area difference
pBCE: Relative breast compliance evaluation
pBRA: Relative breast retraction assessment
PR: Progesterone receptor
pUNR: Relative upward nipple retraction
QoL: Quality of life
SN: Sentinel node procedure
SPSS: Statistical package for the social sciences
